## **5. TRIAL PROCEDURES: RANDOMISATION**

### **5.1. Eligibility**

Eligibility will be based on the uncertainty principle (see Section 3.1). Patients will be eligible if they have a confirmed diagnosis of Parkinson's disease, either early disease (newly/recently diagnosed) or later disease (motor complications).

#### **Early disease randomisation:**

##### **Patients are eligible for the early disease randomisation if:**

- They are newly or recently diagnosed with Parkinson's disease. It is important to ensure the accurate diagnosis of PD and the UK Brain Bank criteria should be used.
- They have functional disability requiring medical therapy. Patients not thought to require dopaminergic treatment at diagnosis may be entered once it is considered that such treatment becomes necessary.
- They are previously untreated for PD or have been treated with dopaminergic PD medication for less than 6 months.
- There is no definite contraindication to, or definite indication for, any of the therapies to which they might be allocated. (If it is considered that LD only is not an appropriate option for a patient, they may be randomised two ways between DA and MAOBI. Similarly, if a MAOBI is not considered appropriate, a patient may be randomised two ways between LD and DA.)
- They are able to complete the trial questionnaires. Non-English speaking patients may be entered if they have a carer, relative or other person who can help them fill in the questionnaires, or if translated documentation is available.

##### **Patients are not eligible for the early disease randomisation if:**

- They have received previous dopaminergic drug therapy for PD for more than 6 months.
- They are demented (as defined by the medical team responsible).
- They are unable to give informed consent.

#### **Later disease randomisation:**

##### **Patients are eligible for the later disease randomisation if:**

- They have PD and develop motor complications that are uncontrolled by LD (either alone or in combination with either a DA or a MAOBI) and hence require the addition of another class of drug.
- There is no definite contraindication to, or definite indication for, any of the therapies to which they might be allocated. (Patients who were already receiving a DA when uncontrolled motor fluctuations arose are not eligible for the DA arm and will be randomised between MAOBI and COMTI only. Patients who were receiving a MAOBI when uncontrolled motor fluctuations arose, or for whom the clinician does not wish a MAOBI to be an option, are not eligible for the MAOBI arm and will be randomised between DA and COMTI only.)
- They are able to complete the trial questionnaires. Non-English speaking patients may be entered if they have a carer, relative or other person who can help them fill in the questionnaires, or if translated documentation is available.

##### **Patients are not eligible for the later disease randomisation if:**

- They are demented (as defined by the medical team responsible).
- They are unable to give informed consent.

**N.B. Patients who have been entered into the early disease randomisation should be re-randomised into the later disease randomisation if motor complications develop that are uncontrolled by drug-dose titration and/or addition of LD if on DA/MAOBI.**

## **5.2. Patient and carer information leaflet**

The conduct of the trial will be in accordance with the Medical Research Council policy on ethical considerations. The patient's consent (according to usual local practice) to participate in the trial must be obtained before randomisation and after a full explanation has been given of the treatment options and the manner of treatment allocation. Patient and carer information sheets and consent form will be provided so that patients and their carers can find out more about the trial before deciding whether or not to participate.

## **5.3. Baseline assessments**

Once the patient has consented to take part, the MMSE should be administered. The patient should be asked to complete the PDQ-39, and EuroQol EQ-5D. The carer, if taking part, should be asked to complete the SF-36.

## **5.4. Randomisation**

Randomisation notepads should be used to collate the necessary information prior to randomisation. Complete the baseline assessments as specified in Table 3 overleaf. The person randomising will need to answer all of the questions before a treatment allocation is given. Patients are entered and randomised into the trial by one telephone call to the randomisation service ([name] free phone from within the UK or [contact][name] from outside the UK) or by [contact] or [name], from outside the UK). Telephone randomisations are available Monday-Friday, 09:00-17:00 UK time. The patient's GP will need to be notified, and a "specimen letter to GP" is supplied.

# **6. TRIAL PROCEDURES: TREATMENT AND FOLLOW-UP**

## **6.1. Drug dosages**

The pragmatic design of the trial allows clinicians to start treatment with whichever drug they prefer as long as it is within the class of drug (i.e. LD, DA, MAOBI or COMTI) to which the patient was allocated at randomisation. Clinicians can give the chosen drug at the dose and scheduling that they normally use and can titrate the dose as they see fit in the best interests of the patient. Drug dosage information is provided and clinicians are referred to the Summary of Product Characteristics (SPC) for each drug for further details.

## **6.2. Treatment modifications**

If disease symptoms are not adequately controlled by the class of drug allocated, after titrating the dose to the maximum tolerated, then it is permissible, as in usual practice, to add a new agent from another class of drugs. In particular, for patients with early disease allocated to a dopamine agonist or MAOBI, levodopa can be introduced as required. Investigators are encouraged to re-randomise patients whose disease is no longer controlled by the class of drug allocated, even with the addition of levodopa, into the later disease randomisation.

Treatment modifications are also permissible if patients are believed to be experiencing adverse effects from a particular drug. A different drug within the same class is preferable - for example, trying a different dopamine agonist - but an agent from a different class of drug can also be used if considered to be in the patient's best interests. Treatment modifications, and the reason for modification, should be recorded on the follow-up forms.

**N.B.** For purposes of follow-up and analyses, patients remain in the PD MED study irrespective of treatment compliance. It is important that questionnaires and study documentation are completed for all patients randomised so that unbiased 'intention-to-treat' analyses can be undertaken.

## **6.3. Other management at discretion of local doctors**

Apart from giving out the trial treatments, all other aspects of patient management are entirely at the discretion of the local doctors. Patients are managed in whatever way appears best for them, with no special treatments, no special investigations, and no extra follow-up visits.

#### 6.4. Follow-up assessments

The principal evaluations will be by means of postal questionnaires to be completed by patients and their carers. These patient-based outcome measures (PDQ-39 and EQ-5D) will be collected at base-line, six months, one year and yearly thereafter (see table 3 below). In addition patients' reports of side-effects will be collected at six months, one year and yearly thereafter and resource use data will be collected at one year and yearly thereafter. The trial follow-up involves minimal administration and paperwork on the part of clinicians and their staff. There is just a simple annual questionnaire to clinicians to ascertain changes in disease status (e.g. onset of motor complications) and changes in therapy. MMSE is measured at baseline and at every subsequent 5 years.

#### 6.5. Serious and unexpected adverse events

Treatment-related toxicity with the drugs and dosages employed in the trial is expected to be minor. For potential toxicities, refer to the Study Product Characteristics for further details. However, to monitor the safety of the drugs used in PD MED, all serious, unexpected adverse events (see footnote A) believed to be due to the PD treatments should be reported to the Trial Office within 48 hours by telephone, e-mail or fax. A detailed report of the event on the Serious Adverse Event Form should be returned to the Trial Office within 7 days. Adverse events that might reasonably be expected to occur in PD patients receiving the trial treatments do not need to be reported in this way but should be recorded on the annual review form, when this form becomes due.

#### Dementia

If the patient becomes demented (as defined by the medical team responsible for the patient) then as much data should be collected as practical during the follow-up period using the EQ-5D, Resource Usage Form and an adapted version of the PDQ-39, called the PDQ-17, which may be completed by the carer. These forms will be sent directly to the patient and carer by the Trial Office. Clinical follow-up information will continue to be obtained from the patient's current doctors.

#### Deaths

A Serious Adverse Event form and an Annual Follow-up form should be completed and returned within two weeks if a patient dies. This information will be supplemented by use of national mortality statistics to monitor long-term survival.

**Table 3 - Baseline & Follow-up assessments**

| Assessment                        | Outcome Measure         | Completed by | At Entry      | 6 Months | 1* Year | 2* Years | 3* Years | 4* Years | 5* Years |
|-----------------------------------|-------------------------|--------------|---------------|----------|---------|----------|----------|----------|----------|
| Functional Status/Quality of Life | PDQ-39, EQ-5D, ICECAP-O | Patient      | ✓             | ✓        | ✓       | ✓        | ✓        | ✓        | ✓        |
| Side effects                      | Side effect form        | Patient      |               | ✓        | ✓       | ✓        | ✓        | ✓        | ✓        |
| Health Economics                  | Resource usage          | Patient      |               |          | ✓       | ✓        | ✓        | ✓        | ✓        |
| Carer well-being                  | SF-36, CES              | Carer        | ✓             | ✓        | ✓       | ✓        | ✓        | ✓        | ✓        |
| Cognitive function                | MMSE                    | Clinician    | ✓             |          |         |          |          |          | ✓        |
| Disease status                    | Follow up form          | Clinician    | Rand. notepad |          | ✓       | ✓        | ✓        | ✓        | ✓        |

\*Assessment schedule years 1 – 5 repeated for all participants until end of trial December 2019 (ie at least 10 years).

**Footnote A "Unexpected"** adverse events are defined as those that would not be expected among elderly patients given anti-parkinsonian medication (which has certain expected side-effects) for Parkinson's disease (which has expected symptoms). For the purposes of this study, **"serious"** adverse events are those which are fatal, life-threatening, disabling or require hospitalisation.

## 7. SIZE OF DIFFERENCE TO BE MEASURABLE

### 7.1. Projected accrual

The PD MED study adopts a pragmatic approach to recruitment aiming to include, if possible, 1500 patients in the early disease randomisation and 1000 in the later disease randomisation. These numbers would give very high statistical power (i.e. over 90% power at  $p < 0.01$ ) to confirm, or refute, even small differences between the different classes of drugs and, should differences emerge, would also be enough to allow meaningful exploration of any differences in the size of benefit between different types of patient, between particular drugs within a class, or over time.

The minimum clinically meaningful difference used for sample-size calculations is 6 points on the PDQ-39 mobility scale. This 6-point difference is based on a study of patients attending neurology clinics with PD who completed the PDQ-39 at base-line and four months later and were also asked to complete 'transition questions' at follow-up. Patients who rated themselves as worse at follow-up, whether in terms of a transition item on physical function or an item on their PD generally, experienced a mean deterioration of 7 points on the PDQ-39 mobility scale. A 6-point change is used in PD MED because it translates more easily into meaningful categories, both of health states and health changes. The mobility scale has 10 items with 5 response categories (ranging from 'never' to 'always') and scores ('0' to '4') are transformed to produce a range 0-100. A 6-point change therefore results if a respondent changes three categories on one item, for example from 'being confined to the house - never' to 'being confined to the house - often'. The same change in score would also result from changing one response category - for example, from 'sometimes' to 'often' - on three of the ten items.

The main analyses in PD MED will compare changes from baseline in PDQ-39 score between groups. The standard deviation (SD) between patients of the 1-year changes in the PDQ-39 mobility dimension in early PD MED data is 18.6. This estimate appears robust, as the SD is about the same for 6-month change and for patients in the early and late randomisations, but is smaller - as, consequently, is the sample size - than the original protocol estimate of 31.6. The earlier estimate was larger because it was based on the between-patient SD seen in an unselected series of neurological clinic attendees with PD. To detect a 6-point difference (i.e. a standardised difference of  $6/18.6 = 0.32$ ) with 90% power at  $p < 0.01$  would require 300 patients in each arm. 155 patients in each arm would give 80% power at  $p < 0.05$ . Thus, although it will be highly desirable for PD MED to randomise a total of 1500 early PD patients and 1000 later PD patients - to improve precision of treatment estimates and for more meaningful subgroup investigations - the study would still have good statistical power to detect small differences with about half as many patients, although subgroup analyses would then only be possible if the treatment differences were of moderate size.

Large-scale recruitment to PD MED should be feasible. There are at least 8,000 new cases of PD diagnosed in the UK each year. If just 5-6% of these were to be randomised between the early PD treatment options, then 1500 patients could be randomised in just 3-4 years. If only 3% of patients were to be entered, 900 could be randomised in the same time scale. The number of patients available for the later disease randomisation should be comparable as most patients diagnosed with PD eventually develop motor complications requiring treatment modifications. The majority of these patients are likely to have received only prior LD, so would be potentially eligible for randomisation between all 3 arms. Some patients (perhaps 20%) will have been previously treated with either a DA or MAOBI, and will only be randomised between MAOBI versus COMTI (if previous DA exposure) or between DA versus COMTI (if previous MAOBI exposure). To recruit 300 patients in each arm, about 1000 patients will need to be randomised (perhaps approximately: DA 300, MAOBI 300, COMTI 400). Again, the study would have good statistical power to detect small differences with about half as many patients.

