**ICECAP-O:** is a new measure of capability in older people for use in economic evaluation. Unlike most profile measures used in economic evaluations, the ICECAP-O focuses on wellbeing defined in a broader sense, rather than health. The measure covers attributes of wellbeing that were found to be important to older people in the UK. It will be evaluated to see if it provides an improved sensitivity in outcome measures for patients with PD compared to the EQ-5D.

**Cognitive function - Mini-Mental State Examination (MMSE):** About 10% of PD patients develop dementia. The trial aims to determine whether therapies prevent or decrease the decline of cognitive function - as measured by MMSE - in PD. MMSE is a well-established 30-point

measure of cognitive function in older people. It is easy to administer, shows good test/retest and inter-rater reliability and performs satisfactorily against more detailed measures of cognitive function. The MMSE is more sensitive than alternative measures at milder levels of cognitive impairment. MMSE score is influenced by sociodemographic status but this will even out in a large randomised study. Levels of 10 to 26 correspond to mild to moderate cognitive impairment in dementia. A score below 10 represents severe disabling dementia and is a milestone from which patients rarely recover.

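### Section 7.1 supports its later-disease power claim with arm totals, not numbers randomised between the two sides: the contingent MAOBI v DA comparison falls short of 90% at p<0.01, and COMTI v MAOBI has little margin for missing data

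*Protocol*

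**What the plan says.** Section 7.1 sets targets of "1500 patients in the early disease randomisation and 1000 in the later disease randomisation" and says of them: "These numbers would give very high statistical power (i.e. over 90% power at" p<0.01. The claim is to confirm or refute even small differences between the drug classes.

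The inputs are a difference of 6 points ("The minimum clinically meaningful difference used for sample-size calculations is 6 points on the PDQ-39 mobility scale") and an SD of 18.6 ("The standard deviation (SD) between patients of the 1-year changes in the PDQ-39 mobility dimension in early PD MED data is 18.6"). For 90% power at p<0.01 the section says this "would require 300 patients in each arm".

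For later disease it adds: "Some patients (perhaps 20%) will have been previously treated with either a DA or MAOBI". These patients enter only a two-way randomisation, MAOBI v COMTI or DA v COMTI. It then projects: "To recruit 300 patients in each arm, about 1000 patients will need to be randomised (perhaps approximately: DA 300, MAOBI 300, COMTI 400". Section 7.1 states no allowance for missing outcomes.

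Section 7.2 pre-specifies two later-disease comparisons: pooled DDI (MAOBI or COMTI) v DA, and COMTI v MAOBI. If one DDI class proves clearly better, that class is then compared with DA.

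**The concern.** The calculation asks for 300 patients on each side of a comparison. The projection delivers 300 in each arm. These are the same only if every patient in both arms could have been allocated to either one. Patients already taking a DA cannot be allocated DA, and patients already taking a MAOBI cannot be allocated MAOBI, so some of each arm's 300 were never randomised against the other class.

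The 300 also sits only slightly above the number needed, with no loss allowance. Outcome comes from postal questionnaires, repeated yearly (section 6.4, Table 3). Section 4.1 says "About 10% of PD patients develop dementia", and section 6.5 moves patients who become demented to an adapted, shorter instrument.

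At stake is how a null result is read. A protocol that promises to refute small class differences at over 90% power invites the reader to treat a non-significant class comparison as evidence of no difference.

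**Working it through.** **Inputs from section 7.1:** difference 6, SD 18.6, 1000 patients, arms DA 300, MAOBI 300, COMTI 400, two-way share 20%. **Assumed:** two-sided tests (this reproduces the protocol's figure; one-sided gives 251 to 255 per arm), and equal allocation within each randomisation option, since no ratio is stated.

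**The protocol's own figure.** n per arm = 2(2.576 + 1.282)² / (6/18.6)² = 286, or 291 with the rounded 0.32. The stated 300 therefore reproduces, slightly generously. Power = Φ(6 / (18.6√(2/n)) − 2.576); at n = 300 this is Φ(3.951 − 2.576) = 91.5%.

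**What the split implies.** Let T be three-way patients, A those in MAOBI v COMTI, B those in DA v COMTI. Section 2.3 gives no other option; Note A of the trial schema is worded more broadly but refers back to 2.3.

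- DA: T/3 + B/2 = 300
- MAOBI: T/3 + A/2 = 300
- COMTI: T/3 + A/2 + B/2 = 400

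The solution is T = 600, A = 200, B = 200, so 40% are two-way. With 20% two-way, shared equally (T = 800, A = B = 100), the arms would be DA 267 + 50 = 317, MAOBI 317, COMTI 267 + 100 = 367.

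**MAOBI v DA (contingent).** Only three-way patients count.

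- 300/300/400 split: 600/3 = 200 per arm. 6 / (18.6 × 0.1) = 3.226. Power is Φ(3.226 − 2.576) = 74.2% at p<0.01 and Φ(3.226 − 1.960) = 89.7% at p<0.05.
- 20% two-way: 800/3 = 267 per arm, power 87.5% at p<0.01.

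**COMTI v MAOBI (pre-specified).** Three-way patients plus group A.

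- 300/300/400 split: 200 + 100 = 300 per side, 91.5%. Loss tolerated before 90% is reached: 1 − 286/300 = 4.7% (3.1% with 0.32).
- 20% two-way: 267 + 50 = 317 per side, 93.1%. Loss tolerated: 9.7%.
- Assumed losses from 300 per side: 10% leaves 270 and 87.9%; 20% leaves 240 and 83.1%.

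**Pooled DDI v DA (pre-specified).** Sum n₁n₂/(n₁+n₂) over the options that contain DA.

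- 300/300/400 split: 400 × 200/600 + 100 × 100/200 = 133.3 + 50 = 183.3. SE = 18.6/√183.3 = 1.37; power 96.3%. The amount needed for 90% is 143.0, so loss tolerated is 1 − 143.0/183.3 = 22%.
- 20% two-way: 97.8%, tolerating about 29%.

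**Early disease, for the fix.** With all 1500 in three-way, each arm has 500. Section 2.2 lets the MAOBI or LD arm be omitted. If, purely for illustration, 40% were two-way, the contingent MAOBI v LD comparison would have 900/3 = 300 per arm and the same 91.5%.

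**The case against.** The strongest reply is that MAOBI v DA is not a planned primary contrast. It arises only if MAOBI clearly beats COMTI, and both pre-specified later-disease comparisons meet the claim before loss (96.3% and 91.5%). That is correct. A reader might infer that the power claim fails for the planned comparisons; before loss, the protocol's figures do not support that. Nor is it true that every other contrast has a margin under 5%: pooled DDI v DA tolerates about 22%. What remains is that section 7.1 makes its claim for differences between classes without restriction, and 7.2 commits to the contingent comparison if its condition is met.

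Second, the arm figures are hedged, and the 20% counts only pre-treated patients. Sections 2.3 and 5.1 also allow the clinician to exclude MAOBI. So 20% and 300/300/400 are not a strict contradiction, and clinician choice may explain part of the gap. But section 7.1 does not say so, and the nearer the true two-way share is to 40%, the nearer the power is to 74%.

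Third, the loss rates of 10% and 20% are assumptions. The dementia figure describes PD patients in general; demented patients are excluded at entry and are still followed if dementia develops. One missed yearly form does not remove a patient from follow-up. All this stands: the documents do not establish what the loss will be. The point is the thin margin and the missing allowance.

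Fourth, p<0.01 is demanding, and at p<0.05 MAOBI v DA still has 90% before loss. That limits the consequence but does not rescue the statement, which is made at p<0.01. This version is dated August 2019, with the trial ending in December 2019, so the value of the correction lies in interpretation, not recruitment.

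**Conclusion.** Wrong as written, in a limited way. The over-90% claim at p<0.01 does not hold for the contingent MAOBI v DA comparison under either reading of the protocol's figures: 74% with the projected split, 87.5% with the stated 20%. For COMTI v MAOBI it holds only while missing data stay below about 5% (about 10% under the 20% share). For pooled DDI v DA it holds with room to spare.

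The conclusion rests on two-sided tests, equal allocation within each option, an equal division of the two-way patients in the 20% case, and counting only patients randomised between the two sides. Comparing all 300 DA with all 300 MAOBI patients would restore 91.5%, but 100 in each arm would not have been randomised against the other class.

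**What to change.** In section 7.1:

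1. State later-disease power separately for each comparison in 7.2, including the contingent one, counting only patients randomised between the two sides and applying a stated loss assumption.
2. Reconcile the 20% with the 300/300/400 split, saying how many two-way entries are expected from prior treatment and how many from clinician choice.
3. Keep the claim of over 90% at p<0.01 only for comparisons shown to meet it. State the two-way share assumed in the early randomisation too, because arms can be omitted there and 500 per arm is not guaranteed for every contrast.

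The cost is a short rewrite and slightly less favourable figures. No extra patients are needed.
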